|--------------------------------------------------------------|--------------------------------------------------------------------------------------------------------------------------------------------------------------------------------------------------------------------------------------------------------------------------------------------------------------------------------------------------------------------------------------------------------------------------------------------------------------------------------------------------------------------------------------------------------------------------------------------------------------------------------------------------------------------------------------------------------------------------------------------------------------------------------------------------------------------------------------------------------------------------------------------------------------------------------------------------------------------------------------------------------------------------------------------------------------------------------------------------------------------------------------------------------------------------------------------------------------------------------------------------------------------------------------------------------------------------------------------------------------------------------------------------------------------------------|
| Adverse Reaction (AR)                                 | 
An untoward and unintended response in a participant to a substance, which is related to any dose administered to that participant.
 
A causal relationship between the administered substance and an AE is at least a reasonable possibility, i.e. the relationship cannot be ruled out.
                                                                                                                                                                                                                                                                                                                                                                                                                                                                                                                                                                                                                                                                                                                                                                                                                                                                                                                                                                                                                                                                                                                          |
| Serious Adverse Event (SAE)                           | 
A serious adverse event (SAE) is any untoward medical occurrence that:
 
 
• results in death
 
• is life-threatening
 
• requires inpatient hospitalisation or prolongation of existing hospitalisation
 
• results in persistent or significant disability/incapacity
 
• consists of a congenital anomaly or birth defect.
 
 
Other adverse events that require medical intervention may also be considered a serious adverse event when, based upon appropriate medical judgement, the event may jeopardise the participant and may require medical or surgical intervention to prevent one of the outcomes listed above. This would include threatened suicide that was prevented by an emergency response. Any planned admissions that were scheduled at the start of the study will not be counted as SAEs.
 
NOTE: The term "life-threatening" in the definition of "serious" refers to an event in which the participant was at risk of death at the time of the event; it does not refer to an event which hypothetically might have caused death if it were more severe.
 
All participants will be prompted to self-report SAEs at the weekly dietitian call. At 12 weeks, we will ask participants about hospitalisation in the last 6 weeks and phone participants who describe an episode to elicit the details.
 |
| Serious Adverse Reaction (SAR)                        | 
An adverse event that is both serious and, in the opinion of the reporting Investigator, believed with reasonable probability to be due to one of the research treatments, based on the information provided.
                                                                                                                                                                                                                                                                                                                                                                                                                                                                                                                                                                                                                                                                                                                                                                                                                                                                                                                                                                                                                                                                                                                                                                                                           |
| Suspected Unexpected Serious Adverse Reaction (SUSAR) | 
All SARs would be deemed SUSARs given neither treatment is expected to cause an SAE.
                                                                                                                                                                                                                                                                                                                                                                                                                                                                                                                                                                                                                                                                                                                                                                                                                                                                                                                                                                                                                                                                                                                                                                                                                                                                                                                                    |

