## 2. Subsequent Visits

Follow-ups will be online only. Participants in both groups will be asked to complete questionnaires and tasks regarding mental health and quality of life and work (**Table 3**). Participants will be asked to weigh themselves, provide saliva (in the morning) and stool samples as outlined above. Two-week and 4-week assessments should take about 5 minutes to complete and the 6-week and 12-week assessment about 30 minutes. In the unlikely event that there are participants that default from completing the online questionnaires and have not contacted us, a researcher will make two attempts within 3-days to phone the participant directly to administer the PHQ-9 (primary outcome) over the phone.

We will invite about 20 participants to a Teams call one-to-one interview to discuss their experiences of trying to follow the diet assigned to them, the support on offer, and the perceived effects of it on their wellbeing. We will select participants to achieve a range based on their adherence to the diet and their response as measured by change in PHQ-9. We will analyse these interviews using simple content analysis. We anticipate interviews lasting up to 30 minutes. We will audio record them prior to analysis then destroy the recordings once the analysis is complete and we are confident of the meaning. The interviews will be audio only because both participants will turn off their video function. This will allow us to use the automatic transcription in Teams to enable us to use anonymised quotes in the write-up.

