### 5. Discontinuation/Withdrawal of Participants

If the participant meets any one of the following conditions, the Investigator will stop the treatment at his/her discretion. The participant, however, will not be considered to have dropped out of the study. This may happen for several reasons, including but not limited to:

- a. The participant wishes to stop the treatment.

- b. The Investigator judges that it is difficult to continue the treatment because of emergence of serious adverse events (SAE) as defined below.
- c. The Investigator judges that the risk outweighs benefit in continuing the treatment.
- d. The participant in the KD arm becomes pregnant.
- e. The Investigator judges that it is inappropriate to continue the treatment for other reasons, such as bereavement.

If a participant wishes to withdraw from follow-up, data collected up to the point of withdrawal will still be used, as detailed in the ePIS. The reason for follow-up withdrawal, if provided, will be recorded on the eCRF. No participants will be replaced if they discontinue treatment or withdraw from follow-up.

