#### Name of drug/substance to be used

A 4:1 (fat: protein+carbohydrates) pre-prepared KD meals and snacks with weekly KD-focused nutritional counselling

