### 3.2. DEFINITION OF POPULATION FOR ANALYSIS

Primary analysis: Given the nature of the study, all randomised participants with at least one measurement on the outcome of interest will be included in the primary intention-to-treat analysis in the group they were randomised.

Safety analysis (serious adverse event): This will include participants who commenced the ketogenic diet compared with all those who commenced the Phyto diet.

The per-protocol population is characterised by:

- health coaches selecting 'Completely/Every Day' or 'Mostly/Most of the Days', when assessing participants' adherence to the diet, in at least 5 out of the (up to) 6 follow-

up calls. (Note on missing data: participants responding to fewer than 5 calls will not be considered adherent)

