## 9. ADVERSE EVENTS

Only a serious adverse event (SAE) occurring to a participant will be collected in this study. Serious adverse events will be presented descriptively

- classified by types,
- the relevance of this SAE to the treatment

We will report serious adverse events (SAEs) only, reporting the total number and the total number of people affected by the arm. We expect these to be very rare and will not use inferential statistics.

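### Apart from suicide risk found through PHQ-9, SAEs in weeks 0–6 are sought only at the weekly treatment call, with no provision for participants who leave the calls

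*Combined protocol and SAP*

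**What the plan says.** Protocol Section I.1, under the SAE definition, names two prompts. During treatment, "All participants will be prompted to self-report SAEs at the weekly dietitian call". Afterwards, "At 12 weeks, we will ask participants about hospitalisation in the last 6 weeks", with a telephone call to anyone who reports an episode.

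The weekly call is itself treatment. Section H describes the ketogenic intervention as "pre-prepared KD meals and snacks with weekly KD-focused nutritional counselling", and Section E gives weekly counselling as the control treatment.

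Section G.5 keeps a person who stops treatment under follow-up: "The participant, however, will not be considered to have dropped out of the study". It does not say whether the weekly calls go on.

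The SAP foresees missed calls. Section 3.2 rules that "participants responding to fewer than 5 calls will not be considered adherent", and Section 4.4 reports sessions attended out of six. If the online questionnaires are not completed, Section G.2 says that "a researcher will make two attempts within 3-days to phone the participant directly to administer the PHQ-9 (primary outcome) over the phone".

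Protocol Section I.2 collects SAEs only. The safety population in SAP Section 3.2 is everyone who commenced either diet, and SAP Section 9 plans "reporting the total number and the total number of people affected by the arm".

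**The concern.** The plan intends to ask all participants, but the asking depends on a contact that a participant can leave while remaining in the trial. Someone who leaves the calls stays in the denominator of the by-arm SAE counts, and no stated question reaches that person's remaining weeks up to week 6. In the table, a participant with no SAE and a participant who was not asked look the same.

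This matters more than usual because non-serious events are not collected, so the SAE counts are the whole safety record. People who feel worse, or who are in hospital, may also be the ones who stop taking calls. One arm follows a 4:1 ketogenic diet while the other adds vegetables and reduces saturated fat, so it is plausible that leaving differs by arm. If it does, the arm that loses more people from the calls would look safer than it is.

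**Working it through.** The plan gives no figure on this point, so there is none to reproduce. The check has two parts.

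**1. Each SAE prompt set against weeks 0–12**

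| Prompt | What it asks | Period covered | Reaches someone who has left the calls? |
|---|---|---|---|
| Weekly call (Section I.1) | Any SAE | Weeks 0–6; look-back of each call not stated | Only if calls continue, which is not stated |
| Week-2, 4 and 6 online assessments (Table 3) | No SAE or hospitalisation item listed | None | Not applicable |
| PHQ-9 item 9 at weeks 2, 4 and 6 (Sections E and I.3) | Suicide risk only | Two weeks each | Yes, by the telephone call in Section I.3; Section E places it at the weekly call |
| Week-12 question (Section I.1) | Hospitalisation | About weeks 6–12 | Yes, but not for weeks 0–6 |

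A participant who takes the last call at week *t* and none afterwards has 6 − *t* weeks with no general SAE prompt. The week-12 question does not reach back to them.

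**2. Possible size**

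Inputs: 88 randomised (SAP Section 2.2), which gives 88 × 6 = 528 person-weeks in weeks 0–6. The share leaving the calls (*d*) and the time of leaving (*t*) are assumptions, because the documents give neither.

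Unprompted share of person-time = *d* × (6 − *t*)/6. If leaving is spread evenly over the six weeks, the mean remaining fraction is 0.5.

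Both arms together:
- *d* = 10%: 0.10 × 1/6 = 1.7% (*t* = 5) to 0.10 × 5/6 = 8.3% (*t* = 1).
- *d* = 20%: 3.3% to 16.7%.
- *d* = 35%, borrowing the attrition allowance in SAP Section 2.2 as an upper value: 5.8% to 29.2%. At *t* = 3 it is 0.35 × 3/6 = 17.5%, or about 92 of 528 person-weeks.

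Arms differing:
- 20% ketogenic, 10% control, all at week 3: 10.0% against 5.0%.
- 30% and 10%, evenly: 0.30 × 0.5 = 15% against 0.10 × 0.5 = 5%.
- 30% and 10%, all at week 2: 0.30 × 4/6 = 20% against 0.10 × 4/6 = 7%.

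If the SAE rate were the same in both arms and unchanged by leaving, and no event surfaced by another route, 30% against 10% leaving evenly would show equal true counts as a ketogenic-to-control ratio of 0.85/0.95 = 0.89. All leaving at week 2 gives 0.80/0.933 = 0.86.

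**The case against.** Several stronger readings are tempting, and the documents do not support them.

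- *The weekly call is the only SAE prompt.* PHQ-9 item 9 is asked at weeks 2, 4 and 6 outside counselling, a positive answer leads to a risk assessment, and an emergency response for serious suicide risk counts as an SAE. The protocol treats self-harm and suicide as a special concern, so this is an important event type. The route covers nothing else, though, and Section E places the assessment at the weekly call, while Section I.3 does not.
- *People who stop the diet are never asked.* The plan is silent on whether calls end when treatment stops. Section I.1 speaks of all participants, and the adherence ratings in the SAP imply calls to people who are not following the diet. An SAE that led the investigator to stop treatment would already be known.
- *A missed call means a lost event.* Someone who misses one call can be asked at the next. The gap is certain only for those who take no later call.
- *The telephone fallback skips the week-12 question.* Section G.7 describes PHQ-9 as the only measure in that call when setting the voucher, but Section I.1 does not say how the week-12 question is delivered.
- *The by-arm ratio is grossly distorted.* A much larger distortion needs a higher SAE rate after leaving, and no such figure is in the documents. A higher rate would also make the true counts unequal, so the resulting factor would not be the ratio that the table displays.

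Table 3 is also weak evidence by itself. It lists outcome measures and omits the week-12 hospitalisation question too, and the questionnaire appendices were not available. The SAP expects SAEs to be very rare and plans no inferential comparison.

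These points narrow the concern without removing it. Section I.1 is where the SAE prompts are set out. Followed as written, it contains nothing that recovers non-suicide events in weeks 0–6 from a person who has left the calls.

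**Conclusion.** The concern holds in this limited form: outside the suicide-risk route, the only general SAE prompt stated for weeks 0–6 is a treatment call, there is no provision for those who leave it, and the week-12 look-back cannot fill the gap. This is a gap in the stated procedure. It is not evidence that events were missed.

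The size is unknown. The 15% against 5% of person-time rests on assumed leaving of 30% and 10%, spread evenly, with no calls afterwards. Equal leaving would lose events without distorting the comparison. The SAP reports follow-up substantially better than predicted, so the 35% value is probably high, although completing an online questionnaire is not the same as taking the calls. With 88 participants and very rare events, the practical question is whether one or two SAEs go unrecorded, which could still change a table that might otherwise show none. The point deserves action because SAEs are the only safety data and the remedy is cheap.

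**What to change.** 1. Put an SAE and hospitalisation question in the week-6 online assessment, sent to everyone including those who have stopped the diet or the calls, with look-back to randomisation.
2. Reword the week-12 question to look back to the last completed SAE prompt, or to randomisation if there was none. This also covers late forms: one completed 7 days late under the present wording would leave 7 of the 42 days after week 6 outside the look-back.
3. Add the same question to the telephone fallback script.
4. In SAP Section 9, report by arm how many participants had complete, partial or no SAE ascertainment, for weeks 0–6 and weeks 6–12 separately.

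The cost is one or two questions on existing forms and one table row, with no new visit. The SAP records that recruitment had already stopped at 88 and does not give follow-up status, so items 1 to 3 may come too late for some or all participants. Item 4 remains possible from the call-attendance records behind SAP Section 4.4. Where follow-up is past, a single catch-up question to those with incomplete calls could be considered, since protocol Section K.6 keeps contact details until publication; any such contact would need to fit the approvals in place.

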The current study proposes to test whether a 6-week ketogenic diet is an effective treatment for treatment-resistant depression. We will aim to recruit around 100 participants with treatment-resistant depression. On completion of baseline assessments, participants will be randomised 1:1 into the KD group or control group. The KD group involves 6-week pre-prepared ketogenic diet (i.e. the ratio of fat to protein and carbs is 4:1) with weekly KD-focused behavioural and nutritional counselling. The control group will receive weekly nutritional counselling to increase vegetable consumption and reduce saturated fat intake. Participants in the control group will receive food vouchers (£20 every two weeks) to help purchase these items. This aims to be a plausible placebo dietary treatment for depression. Usual treatment for depression will continue, and a leaflet material is provided in both groups (**APPENDIX 9. Dietary materials for the intervention group** and **APPENDIX 10. Dietary materials for the control group**). The primary outcome will be assessed by the difference between groups in the change in self-reported depression severity, using the Patient Health Questionnaire-9 (PHQ-9) (**APPENDIX 8. SELF-REPORTED QUESTIONNAIRES**) at 6 weeks. The secondary outcomes are anxiety score, ability to experience pleasure, work and social adjustment, quality of life, and cognitive performance (**APPENDIX 8. SELF-REPORTED QUESTIONNAIRES**) from baseline to 6 weeks. This trial will also investigate potential mechanistic pathways (i.e. changes in cortisol and gut microbiome) that may explain the effect of a KD on depressive symptoms. We will follow participants to 12 weeks to assess whether they are following the assigned diet and the changes in primary and secondary outcomes.

In this study, a special concern is risk of self-harm and suicide, and further assistance and monitoring are in place. PHQ-9 will be completed every two weeks in the first six weeks and asks participants 'Over the last two weeks, how often have you been bothered by thoughts that you would be better off dead, or of hurting yourself in some way?'

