with response options 'Not at all, several days, more than half the days, nearly every day.' Participants that report that they have had such thoughts more than half the days or nearly every day will have their risk of suicide assessed at the weekly telephone call using the procedure outlined in **Section I. Safety** and Error! Reference source not found.. Anyone judged to have a serious risk of suicide where an emergency response is initiated will be counted as having a serious adverse event.

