**Table 3: Study schedule and follow-up assessments**

| Outcome measures | Baseline assessment (consent to the study) | 2 weeks follow-up assessment | 4 weeks follow-up assessment | 6 weeks follow-up assessment | 12 weeks follow-up assessment |
|------------------|--------------------------------------------|------------------------------|------------------------------|------------------------------|-------------------------------|
| PHQ-9            | ✓                                          | ✓                            | ✓                            | ✓                            | ✓                             |
| GAD-7            | ✓                                          | ✓                            | ✓                            | ✓                            | ✓                             |
| SHAPS            | ✓                                          |                              |                              | ✓                            | ✓                             |
| PDQ-5            | ✓                                          |                              |                              | ✓                            | ✓                             |
| SF-12            | ✓                                          |                              |                              | ✓                            | ✓                             |
| WSAS             | ✓                                          |                              |                              | ✓                            | ✓                             |

|                                                    |   |  |  |   |   |
|----------------------------------------------------|---|--|--|---|---|
| PILT                                               | ✓ |  |  | ✓ | ✓ |
| Substance use and health-related absence from work | ✓ |  |  | ✓ | ✓ |
| Weight                                             | ✓ |  |  | ✓ | ✓ |
| Height                                             | ✓ |  |  |   |   |
| Saliva/Stool samples                               | ✓ |  |  | ✓ |   |
| Interview                                          |   |  |  |   | ✓ |

Note: PHQ-9, Patient Health Questionnaire-9; GAD-7, General Anxiety Disorder Scale; SHAPS, Snaith-Hamilton Pleasure Scale; PDQ-5, Perceived deficits questionnaire-5-item; SF-12, SF Short-Form 12 Health Survey; WSAS, Work and Social Adjustment Scale; PILT, Probabilistic instrumental learning task.

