#### 4.4. PROCESS OUTCOMES

The following outcomes will be presented descriptively

| Objectives                                | Outcome Measures                                                                                                                                                                                                                                                                 | Time point(s)          |
|-------------------------------------------|----------------------------------------------------------------------------------------------------------------------------------------------------------------------------------------------------------------------------------------------------------------------------------|------------------------|
| Intervention engagement            | Proportion of sessions attended (Numbers of attended/6)                                                                                                                                                                                                                          | Baseline, week 6       |
| Dietary adherence score            | The percentage of health coaches selecting 'Completely/Every Day' or 'Mostly/Most of the Days' when assessing participants' adherence to the diet.                                                                                                                               | Weeks 1, 2, 3, 4, 5, 6 |
| Ketone levels                      | 
 
- the percentage of achieving ketosis level of 1.5 mmol/L and above
 
- the percentage of achieving ketosis level of 4 mmol/L and above
 
- the percentage of achieving ketosis level of median mmol/L and above
 
 | Weeks 1, 2, 3, 4, 5, 6 |
| Diet adherence after intervention  | Self-reported adherence to KD at each time point "Are you still following the diet that the dietitian advised you to follow?"                                                                                                                                                    | Week 12                |

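### After the six weekly calls, the only direct SAE question in the main text is about hospitalisation, which is narrower than the protocol's own SAE definition, and the SAP does not split SAEs by period

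*Combined protocol and SAP*

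**What the plan says.** Protocol Section I.1 sets out how SAEs are found. During treatment, "All participants will be prompted to self-report SAEs at the weekly dietitian call". SAP section 4.4 counts sessions attended out of six and rates adherence in weeks 1 to 6, so there are six such prompts. For the later period the next sentence of Section I.1 reads "At 12 weeks, we will ask participants about hospitalisation in the last 6 weeks", and those who describe an episode are phoned for details.

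The definition in the same section goes beyond admission. It lists life-threatening events and lasting disability or incapacity. It also allows other events that need medical intervention to count, "based upon appropriate medical judgement", and adds: "This would include threatened suicide that was prevented by an emergency response".

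Suicide risk has a second route. Section E says "PHQ-9 will be completed every two weeks in the first six weeks"; Table 3 ("Study schedule and follow-up assessments") and SAP Table 1 add week 12. Under Section I.3, the two most frequent of the four answers to item 9 lead to a telephone risk assessment, and the flow chart applies after every PHQ-9. Section E adds: "Anyone judged to have a serious risk of suicide where an emergency response is initiated will be counted as having a serious adverse event".

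SAP section 9 reports SAEs descriptively by type and relevance to treatment, with totals of events and of people by arm. It names no time window and no split by period.

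**The concern.** The week-12 question is narrower than the definition it serves, and one class of event it omits is a non-admitted suicide emergency, in a trial that names self-harm and suicide as its special concern. Section I.2 collects no non-serious adverse events, so no other adverse-event data would reveal an SAE that was missed.

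Weeks 6-12 are not necessarily free of exposure. Section H provides for participants who wish to stay on the diet, and SAP section 4.4 asks about continued adherence at week 12. Section I.2 also starts the expedited reporting periods when the principal investigator becomes aware of a reaction, so an event that never surfaces starts no clock.

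At stake is what the SAE table can say about the six weeks after meals and calls stop. A low count there could mean few events or narrower questions.

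**Working it through.** No figure in the plan is in dispute, so the check is a count of which scheduled question covers which weeks.

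**Inputs**
- Any-SAE prompt: weekly calls, weeks 1 to 6 (Section I.1; SAP 4.4).
- Hospitalisation question: week 12, six-week look-back (Section I.1).
- PHQ-9 item 9: weeks 2, 4, 6 and 12 after baseline (Table 3; SAP Table 1), two-week look-back (Section I.3).

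**Coverage per participant**

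| Route | Weeks 0-6 | Weeks 6-12 |
|---|---|---|
| Any-SAE prompts | 6 | 0 |
| Weeks covered by the hospitalisation question | not used | 6 of 6 |
| Item 9 forms | 3 | 1 |
| Weeks covered by item 9 | 6 of 6 (0-2, 2-4, 4-6) | 2 of 6 (10-12) |

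Weeks after treatment with no question, direct or indirect, that would reach a non-admitted SAE: 6 − 2 = 4, about weeks 6-10. For a non-admitted SAE unrelated to suicide, item 9 does not help and the gap is all 6 weeks.

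**What item 9 adds.** It asks about thoughts, not events, and prompts a call only at its two highest answers. An emergency in week 8 that had settled by week 10 would not be expected to trigger it.

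**Which suicide emergencies fall in the gap.** The Section E rule closes a description of the trial's own process: item 9, then risk assessment, then an emergency response. The team knows of any event reached that way. For an emergency handled by family, a GP or a crisis service, the Section I.1 wording applies, and that leaves SAE status to medical judgement.

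**Illustration only.** Assume a constant hazard over 12 weeks, full reporting at the six calls, and a suicide-related SAE without admission that is handled by others and not volunteered. If item 9 and the risk call pick up a share p of such events in their two-week window, the share captured is (6 + 2p)/12:
- p = 0: 6/12 = 50%
- p = 0.5: 7/12 = 58%
- p = 1: 8/12 = 67%

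For non-admitted SAEs unrelated to suicide, the share stays at 50%. The documents give no event rate, so none of this converts to a number of events among the 88 randomised (SAP 2.2).

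**The case against.** Close monitoring on treatment and lighter monitoring afterwards is a recognisable, proportionate choice for a six-week diet, and the protocol states both stages openly in consecutive sentences. Week 12 is not bare: the PHQ-9 is repeated, the suicide flow chart applies, a researcher phones the next working day where item 9 requires it, and health-related work absence is asked about, an indirect sign of incapacity. The week-12 form, the flow chart and the suicide assessment manual were not available, and any of them might ask about emergency attendance or recent crises. SAP section 9 expects SAEs to be very rare and plans no inference.

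Most of this stands, and it is why the point is minor. It narrows the gap without closing it: on the main text, about weeks 6-10 still have no scheduled question on non-admitted SAEs.

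Three stronger readings are tempting and not supported:
- A reader might infer that every suicide emergency without admission after week 6 would be lost. Those the trial team responds to itself are already known to it, and others may be volunteered.
- A reader might take the SAP to say that the two periods are pooled. It says only that totals are given by arm. Combination is the natural reading, because collection runs to week 12, but it remains an inference.
- A reader might infer that the difference in questioning is hidden. The protocol discloses it; the weakness is that the planned SAE summary does not carry it through.

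**Conclusion.** The point holds in a limited form and is minor. The gap is confined to non-admitted SAEs in weeks 6-12 that were handled outside the trial and not reported spontaneously, with partial, indirect cover in about weeks 10-12 for suicide-related events only. As naturally read, the SAP total would combine six weeks of prompting for any SAE with six weeks in which only hospitalisation is asked about directly.

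A reader might go further and infer a bias between arms. The documents do not support that: the questions and timing are the same in both arms. Nor is the week-6 primary outcome affected. The number of missed events cannot be estimated and may be zero.

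The conclusion assumes that the appendices add no broader SAE question at week 12. If they do, the ascertainment gap shrinks or closes, and one sentence saying so would settle that part.

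**What to change.** 1. **Week-12 question.** For anyone still to answer it, ask about any SAE in the last six weeks, naming self-harm, suicide attempt, and any emergency or crisis-team response without admission. Keep the same phone follow-up. The cost is one reworded question and perhaps a few more calls.

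   This may reach few people or none. Recruitment had stopped at 88. If SAP version 4.0 is dated 12 December 2024 (the year is assumed from version 3.0), only people randomised after 19 September 2024 (84 days earlier) would not yet have reached week 12. If follow-up also kept to the anticipated end date of 31 December 2024, the last randomisation was by 8 October 2024, a window of 19 days. Randomisation dates are not given. If nobody remains, drop this step.

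2. **SAP section 9.** Report SAEs by arm separately for weeks 0-6 and 6-12, and state what was asked in each period. If the week-12 wording changes, say who answered which version, so that a third pattern of questioning is not added unseen. The cost is one split in a table and a sentence or two. It recovers no missed event, but it works even if follow-up is complete and lets the later count be read for what it is.
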